### Secondary Outcome Measures

Reasons for failure to attend the scheduled 7-day post-operative visit will be evaluated as a secondary outcome measure. These reasons will be determined by administering a questionnaire in person at baseline to all participants, followed by a similar questionnaire by phone call at 42 days to a sub-sample of participants who fail to return for the 7-day visit.

# STUDY DESIGN

## Overview of Study Design

The proposed study is a randomized controlled trial. Men who will have undergone voluntary medical male circumcision will be approached for study enrollment. Participants will be randomized to receive either the intervention (context-sensitive text messages after circumcision) or the control condition (usual care). Participants in the intervention arm will receive text messages as described in section 5 below. All participants will be followed up for a total of 42 days.

## Study Setting

This study will be conducted in Kisumu. Kisumu is the third largest city in Kenya and is located in Nyanza province, which is in western Kenya on Lake Victoria. Kisumu city has a population of approximately 400,000. The majority of Kisumu residents belong to the Luo ethnic group, one of the largest tribes in Kenya. The Luo are traditionally a non-circumcising community. The fishing community in Kisumu has a very high prevalence of STIs including HIV [21, 22]. Nyanza is also the province in Kenya where programmatic implementation of voluntary medical male circumcision has been launched by the Ministry of Health and is being brought to scale.

## Study Population

Participants for this study will be recruited from among men who will have undergone circumcision at selected sites in Kisumu East and West operated by the Nyanza Reproductive Health Society. The precise clinics where we will conduct the study will be determined once we are in the field, but the performance site for the study is the Nyanza Reproductive Health Society, which performs male circumcision at 16 fixed and mobile sites in Kisumu East and West.

## Inclusion Criteria

Participants who meet the following criteria will be eligible for enrollment:

1. Male
2. 18 years or older
3. Have undergone circumcision on the day they are screened for the study
4. Currently own a mobile phone with text-messaging capability, and
5. Have the mobile phone in their possession at the time of enrollment
6. Able and willing to respond to a questionnaire administered via a phone call

## Exclusion criteria

Participants who meet the following exclusion criteria will **not** be eligible for enrollment:

1. Prior participation in a study on male circumcision
2. Currently participating in other ongoing research studies
3. Any medical condition or situation exists such that study participation would not be in the man’s best interest, as determined by the investigator

# METHODOLOGY

## Treatment Assignment Procedures

### Randomization Strategy

All enrolled participants will be randomized to receive either the intervention condition (text message) or control condition (no text message; standard of care) in a ratio of 1:1 after giving informed consent for the study.

### Sequence generation

A block randomization scheme with variable block sizes will be generated using STATA 10.1 ralloc.ado module v3.5.2 [23]. This will ensure approximately equal sample sizes, and that participants and study staff cannot anticipate assignment to either group. Treatments will be allocated in 1:1 ratio. All the study investigators and staff will be blinded to the block number, block size and sequence in the block. The treatments will be assigned via pre-prepared sealed, opaque envelopes and the envelopes will be ordered in the sequence of treatment assignments generated by the STATA code. Once eligibility for randomization has been determined, the first available allocation envelope will be assigned to the study subject. The subject will be randomized to the treatment arm indicated inside the envelope.

### Allocation concealment

As potential subjects are identified, a research assistant will be notified to assess eligibility. Once a subject is deemed eligible for enrolment, has given the necessary informed consent, has been enrolled, has responded to a brief questionnaire, and has had his demographic information abstracted from his clinic records, the research assistant will issue the next in a series of sequentially numbered, sealed, opaque envelopes containing group assignment [24]. The participant’s clinic number will be written on the envelope, and the participant will be required to open and read the treatment assignment in the presence of the research assistant, who will then enter the group assignment into a database and store the envelope. If a participant is unable to read, the research assistant will read the group assignment on his behalf.

### Implementation of Randomization Procedures

A biostatistician assigned to the study from the Biometrics Core of the Center for AIDS Research at the University of Washington will carry out randomization procedures in Seattle, USA. The biostatistician will not be involved in any other aspects of conducting the study. The sequentially numbered, opaque sealed envelopes containing group assignment will be shipped to by the biostatistician from Seattle to the study coordinator in Kisumu via FedEx. The study biostatistician will retain the key to treatment assignments. The study coordinator will be on site every day to ensure compliance with the study protocol.

### Blinding

Because of the nature of this intervention, it will not be possible to blind the participants to the group assignments. Clinicians and nurses conducting MC procedures and follow-up will, however, not be aware of study group assignment.

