## Study Outcome Measures

### Primary Outcome Measures

The primary outcome measure for objective 1 is the proportion of men failing to return for a post-operative clinic visit at 7 days. This proportion will be determined by examining each participant’s clinic records after their 7th post-operative day. Adherence to this clinic visit will be analyzed as a dichotomous variable. Participants will be considered to have ‘attended’ or ‘not attended’ the clinic visit after the elapse of 3 days after the scheduled 7-day visit.

The primary outcome measure for objective 2 is the proportion of men who report resumption of sexual activity before 42 days post-circumcision. This proportion will be determined by self-report using a brief questionnaire delivered via SMS. The analysis will be as a dichotomous variable, with participants considered as having either ‘resumed’ or ‘not resumed.’ Among men who resume sex before 42 days post-circumcision, we will also compare the time to resumption by study arm.

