## Final Study Visit (Virtual Visit)

At 42 days post-procedure, a final intervention text message will be sent to participants randomized to the intervention arm. After the final SMS at day 42, participants in both arms will be interviewed via phone call to determine outcome data for our second primary objective (appendix IV). All participants will also be invited to visit the clinic should they wish to receive free condoms

At conclusion of the randomized controlled trial, a subset of participants who failed to return for the scheduled 7-day post-operative visit will be invited to take part in a phone interview to ascertain reasons for failure to return. A brief questionnaire (similar to the baseline questionnaire, appendix III) will be administered via phone interview. Items in this questionnaire will allow for assessment of secondary study outcome measures. Responding to this questionnaire will terminate study participation.

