# DATA COLLECTION AND MANAGEMENT

## Data Collection

Enrollment data will be directly entered into an electronic database as it is collected during the enrollment visit. A study data clerk will be assigned to enter all such data.

All data collected at the 7-day visit will be abstracted from clinic records directly into an electronic database by a study data clerk. Data abstraction for the 7-day visit will be a continuous process and will occur immediately after the expiry of the 7-day post-MC period. We will develop electronic forms that will allow for this process.

For the final follow-up virtual visit (interview at day 42), responses from the questionnaire administered via phone call will be recorded by study staff into an electronic database. If a participant fails to respond to the phone call, study staff will retry twice daily for one week (7 days). If a response is not received by this time, the participant will be considered lost to follow up due to inability to collect data on the final outcome measure. Data entry will be done by designated study staff that will have undergone training.

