# STUDY LIMITATIONS

Due to the nature of the intervention, it will not be possible to blind participants to study group assignment. However, clinicians and nurses involved in the routine care of the participants will be blinded, unless participants disclose to them.

Resumption of sexual intercourse at 42 days will be recorded based on self-reports. Since there is no feasible biological surrogate marker for this measure, our results may be affected by social desirability bias since participants may have a tendency not to report early resumption of sex.

This study will exclude men who do not own or have access to a mobile phone. There may be some selection bias because younger men as well as poor men are less likely to have phones. This may affect the generalizability of results. However, the majority of men in the age-group targeted by the MC intervention already own mobile phones, or have access to one. Furthermore, mobile phone access in general is rapidly expanding, and we expect this not to be a major limitation.

Contamination: It is possible that men in the intervention arm may share messages with friends receiving usual care. However, it is unlikely that such men will be circumcised on the same day.

If participants share phones with others, there exists the potential for exposing personal information to others. However, the study will not send out any sensitive personal health information. Further, study procedures will be thoroughly explained to participants and they will be consented only if they fully understand study procedures and find the messages acceptable to them.

At day 42, recall bias related to resumption of sexual intercourse may also interfere with accuracy of results. However, because the duration of interest is relatively brief, we expect recall to be accurate.

Lost phones or changed phone numbers: Participants will be asked for an alternate phone number, if available. This number would then be used for the final interview should calls to the primary number fail.

Some participants may seek follow-up care at non-participating centers closer to their homes. Participants will be educated to return to the circumcising centers for all follow-up care. Since the clinic number on a patient’s record is a unique identifier across all MC sites operated by the NRHS, patients who seek care at any one of these sites will be identified and their records captured.

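### The protocol masks clinicians and nurses but does not mask the staff who conduct the day-42 interview, although the second primary outcome is an unverifiable self-report

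*Protocol*

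**What the plan says.** **Who is masked.** Under Blinding (section 5.1), participants cannot be masked, but "Clinicians and nurses conducting MC procedures and follow-up will, however, not be aware of study group assignment". Study Limitations (section 11.0) names the same two groups: "clinicians and nurses involved in the routine care of the participants will be blinded, unless participants disclose to them".

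**What study staff are masked to.** Sequence generation (section 5.1) states: "All the study investigators and staff will be blinded to the block number, block size and sequence in the block". This protects the next allocation. It does not hide an arm once assigned.

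**Who learns the arm.** Under Allocation concealment (section 5.1), the participant opens the envelope in front of the research assistant, "who will then enter the group assignment into a database and store the envelope". The assistant reads the assignment out if the man cannot read. In the schematic of section 5.2, the registration SMS also carries the study arm.

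**Who obtains the second primary outcome.** Section 6.4 says that "participants in both arms will be interviewed via phone call to determine outcome data for our second primary objective". Section 9.1 adds that "responses from the questionnaire administered via phone call will be recorded by study staff into an electronic database". Neither section mentions masking, or says that callers differ from the staff who enrolled and randomised the man.

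**What bias is acknowledged.** Section 11.0 concedes that no feasible biological marker exists for this outcome and that "our results may be affected by social desirability bias since participants may have a tendency not to report early resumption of sex". It does not mention interviewer bias.

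**A conflict on mode.** Primary Outcome Measures says of the same outcome: "This proportion will be determined by self-report using a brief questionnaire delivered via SMS". The section 5.2 schematic, the opening of section 6.0, and sections 6.4 and 9.1 all say phone call.

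**The concern.** The people whom the protocol masks are not the people who collect the day-42 outcome. That outcome is one man's answer, given in conversation, on whether he had sex before he was advised to. Nothing can verify it. How a question is put, how far a hesitant answer is probed and how an ambiguous one is coded are all in the caller's hands. A caller who knows that the man was sent abstinence messages could handle these steps differently by arm, without intending to.

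Participants cannot be masked, so some differential reporting may remain whatever is done. The caller's knowledge of the arm is a component that the study can reduce. The planned sensitivity analyses (section 10.2) impute missing answers. They do not address answers that were obtained but recorded differently by arm, so such an error could not be separated from a real effect afterwards.

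**Working it through.** **Step 1. Roles set side by side**

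| Role | Contact with the day-42 outcome | Masked to arm? |
| --- | --- | --- |
| Clinicians and nurses | None stated | Yes (Blinding; section 11.0) |
| Research assistant | Not stated whether he or she also makes calls | No: sees the arm and enters it |
| Study staff making and recording day-42 calls | Collect the outcome | Nothing stated |

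The one role that certainly collects the outcome is the one on which the masking text is silent. The arm sits in a study database, and nothing says that callers work without it.

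**Step 2. Reproduce the plan's own figure**

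Inputs from section 10.1: control proportion p0 = 0.225; RR 0.70, so p1 = 0.225 × 0.70 = 0.1575; two-sided 5% (z = 1.96); 80% power (z = 0.84); 1:1 allocation.

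n = [1.96 √(2 p̄(1 − p̄)) + 0.84 √(p0(1 − p0) + p1(1 − p1))]² / (p0 − p1)², with p̄ = 0.19125.

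- √(2 × 0.19125 × 0.80875) = 0.5562
- √(0.225 × 0.775 + 0.1575 × 0.8425) = 0.5541
- n = (1.96 × 0.5562 + 0.84 × 0.5541)² / 0.0675² = 531.1, rounded up to **532 per arm**, as stated.

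The inputs and the test are therefore read as the plan intends. Masking callers changes neither the sample size nor the power.

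**Step 3. Illustrate differential recording with no true effect**

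Let the true proportion be 0.225 in both arms, and let a net fraction u of SMS-arm resumers be recorded as non-resumers beyond any such loss in the control arm. The fraction u is an assumption; the protocol gives no value. The recorded SMS proportion is p_t = 0.225(1 − u). With d = 0.225 − p_t and n = 532:

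P(reject) = Φ[(d − 1.96 s0)/s1] + Φ[(−d − 1.96 s0)/s1],

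where s0 = √(2 p̄(1 − p̄)/n), p̄ is the mean of the two recorded proportions, and s1 = √([0.225 × 0.775 + p_t(1 − p_t)]/n).

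For u = 0.10: p_t = 0.2025, d = 0.0225, p̄ = 0.21375, s0 = 0.02514, s1 = 0.02513. The arguments are −1.065 and −2.856, giving 0.1434 + 0.0021 = 0.1455.

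| Assumed u | Recorded RR | P(significant), no true effect |
| --- | --- | --- |
| 0 | 1.00 | 5.0% |
| 5% | 0.95 | 7.3% |
| 10% | 0.90 | 14.6% |
| 15% | 0.85 | 27.3% |
| 20% | 0.80 | 44.7% |

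Ten per cent is about 12 men: 532 × 0.225 = 119.7 expected resumers in the arm, of whom 10% is 12.0.

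**Step 4. The opposite direction**

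Suppose the true RR is 0.70 but 10% more resumption is recorded in the SMS arm (again an assumption), for example because callers probe those men harder. Then p_t = 0.1575 × 1.10 = 0.17325, d = 0.05175, s0 = 0.02449 and s1 = 0.02443. The first argument is (0.05175 − 0.04799)/0.02443 = 0.154, so power is about 56% instead of 80%; the other tail is negligible.

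**The case against.** **The protocol is silent; it does not say that callers are unmasked.** This stands. A reader might infer that the day-42 interviewers know the arm. Only the research assistant is shown to learn it, and section 9.1 speaks of study staff in general. Overlap is possible but not stated. The supportable statement is that no masking of callers is specified, in a protocol that does list who is masked.

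**The direction is not known.** This stands too. A reader might infer that the error must favour SMS. Steps 3 and 4 show that easier acceptance and harder probing of SMS-arm answers push opposite ways, and the documents do not say which would dominate.

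**The figures do not isolate interviewer bias.** Correct. They describe any net differential, including the participants' own social-desirability bias, which masked callers would not remove. Nor does a 30% differential show anything further: it gives the design RR of 0.70, and hence 80% power, by construction.

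**Attendance at day 7.** A reader might extend the point to the first primary outcome, since no masking is stated for the abstracting data clerk either. The documents do not support that. Attendance is a dated visit in routine clinic records, kept by clinicians who are to be masked and classified by a set window, so abstraction leaves little room for judgement.

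**The outcome may not come from a call at all.** If the questionnaire went by SMS, as Primary Outcome Measures says, interviewer bias would largely not arise. But the operational sections say phone call, and inclusion criterion 6 requires willingness to answer by phone. The concern survives, and the conflict needs resolving.

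**Masking would be imperfect.** SMS-arm men receive messages on days 41 and 42, shortly before the call, so some will disclose their arm. This limits the benefit without removing it.

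**Conclusion.** The point holds for the day-42 outcome. As written, the protocol permits the self-reported second primary outcome to be collected by staff who know the arm, and it specifies no safeguard. This is an avoidable risk of differential recording, of unknown size and direction; it is not a demonstrated bias.

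The scale is illustrative and rests on assumptions: no true effect, 22.5% in both arms, 532 men per arm, and an assumed net 10% relative under-recording in the SMS arm from any cause. On these, the false-positive rate rises from 5% to about 15%; over assumed values of 5% to 20% it runs from about 7% to 45%. How much of any such differential would come from callers knowing the arm cannot be learned from the documents. The sample-size figures are unaffected. The weight is that of a low-cost improvement to a primary outcome measure.

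**What to change.** State the following under Blinding and in sections 6.4 and 9.1:

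- Day-42 call lists and interview forms carry no arm field.
- Where possible, each man is called by an existing staff member who did not randomise him.
- The resumption items follow the fixed questionnaire wording (appendix IV) and are recorded before any discussion of messages.
- The interviewer records any disclosure of arm, so that the extent of unmasking can be reported.

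Reconcile Primary Outcome Measures (questionnaire by SMS) with the section 5.2 schematic, the opening of section 6.0, and sections 6.4 and 9.1 (phone call).

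The cost is hiding one database field and some care in assigning calls. The documents give no staffing numbers, hence the qualifier on who calls. The downside is that masking will be partial, because some men will reveal their arm. No change to sample size, power or analysis is needed.

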## STUDY INTERVENTION/TEXT MESSAGING PROTOCOL

### Schematic of text messaging protocol:

**Demographic Information Module**

Abstract demographic information from participant’s clinic file into electronic database

**Study Registration Module**

SMS-based registration: SMS containing *Study Arm, time to send SMS, preferred language*

**Text Messaging Module (days 8, 14, 21, 28, 35, 41 and 42)**

**Response within 1 week**

No Response

Loss to follow-up

**Enrollment Module (SMS-based registration)**

Assign Study ID number

Complete electronic enrollment form

Participant found eligible; informed consent obtained

**Day 7 (+/- 3 day window)**

Abstract data from participant’s clinic records into electronic database

**Day 42 (+ 7 day window)**

Administer questionnaire via phone call

Randomization to study arms

**Allocation to intervention (n=600)**

**Allocation to control (n=600)**

**Text Messaging Module (days 1,2,3,4,5,6,7)**

### Rationale for Selecting Intervention and Control Conditions

Several potential study arms were considered before finally selecting the intervention (personal phone and text messaging) and control (personal phone and no text messaging) groups. The table below summarizes the pros and cons of several different intervention and control choices:

|  | **PROS** | **CONS** |
| --- | --- | --- |
| **Intervention:**  Personal Phone + SMS  **Control:**  Personal Phone + No SMS (usual care) | - Removes study-issued phone as a potential reminder (isolates effect of SMS alone) - Minimal extra cost for scale up - Easier to integrate to existing programs and bring to scale - Less expensive study - Closer to an effectiveness study as relates to men with phones | - Excludes men without phones (generalizable only to men with phones) - May substantially reduce size of eligible population due to phone ownership - Exposing sensitive personal information if phone is shared and not owned |
| **Intervention:**  Study Phone + SMS  **Control:**  Study Phone + No SMS | - Phone acts as incentive for study retention for both groups - Isolates the effect of SMS | - Study phone a powerful reminder - Affordable study but adds substantial cost to MC - Limits ability to disseminate - Unlikely to be implemented widely due to cost (everyone may say that they don’t have a phone) |
| **Intervention:**  Study Phone + SMS  **Control:**  No Phone + No SMS + Study Phone at 42 days | - Study phone acts as incentive for study retention for intervention arm | - Study phone itself is a powerful reminder - Affordable study but adds substantial cost to MC - Hard to tell if any benefits are due to SMS or phone |
| **Intervention:**  Study Phone + SMS  **Control 1:**  Study Phone + No SMS  **Control 2:**  Usual care (No Study Phone + No SMS) | - Gives study ability to analyze effect of phone vs. effect of SMS - If successful, would guide programs on whether to buy phones or not for best results | - Larger sample size - Affordable study but adds substantial cost to MC |
| **Intervention:**  Study Phone + SMS  **Control 1:**  Study Phone + Sham SMS  **Control 2:**  Study Phone + No SMS  **Control 3:**  Usual care (no phone + no SMS) | - Ability to detect whether differences are due to **content** of SMS | - Larger sample size - Study phone a powerful reminder - Sham SMS also a strong reminder - Affordable study but adds substantial cost to MC |

